# Population

## Inclusion criteria

Patients > 18 and < 85 years old

Patients hospitalized with a laboratory-confirmed SARS-CoV-2 infection

Patients on oxygen therapy (nasal cannula, mask or high-flow nasal oxygen therapy)

Patients able to self-position to the prone position or with minimal assistance of one person

Signed the consent form

Patients hospitalized in COVID-19 medical ward for < 72 hr

## Non-inclusion criteria

Patients on oxygen therapy or continuous positive airway pressure or non-invasive ventilation at home

Patients with COPD (Gold stage 3 or 4)

Patients with known chronic diffuse interstitial lung disease

Patients with a chronic neuromuscular pathology

Contraindication to prone position (recent thoracic trauma, pneumothorax, unstable spine or pelvis fractures etc.)

Deep vein thrombosis or pulmonary embolism with curative anticoagulation for < 48 hr

Hemodynamic instability (mean arterial pressure < 65 mm Hg) persisting for > 1 hr

Respiratory rate > 40 cycles/min

Excessive use of accessory respiratory muscles (as determined by the clinician)

Indication for curative non-invasive ventilation (acute pulmonary edema or acute hypercapnic respiratory failure)

Intestinal occlusive syndrome

Patients unable to protect upper airway

Patients discharged from intensive care after having treatment with invasive or non-invasive ventilation for COVID-19

Inability to understand French or to follow instructions to perform awake PP

Patients not affiliated or excluded from the French social security system or under law protection (namely minors, pregnant or breastfeeding women, persons deprived of their liberty by court or administrative decision)

Do not intubate order

## Recruitment procedure

Patients will be recruited in the "COVID" departments (excluding ICUs) of the hospitals participating in the study.

Participation in the study will be possible as soon as the patient presents a SARS-CoV-2 infection and is hospitalized in a medical ward dedicated to COVID-19 patients.

The information and written consent of the patients will be obtained on admission to the ward, and a copy of the information note and consent form will be given to the physician or physiotherapist personally.

The patient will be able to decline to participate in the study and the treatment will not be modified.

The patient will be free to decline the use of the data collected during the intervention and the care provided will not be modified.

## Risk/benefit

### Benefits of prone position during spontaneous breathing

Ding et al. (DING, Crit Care, 2020) showed that PP could increase the P/F ratio by 25 to 35 points as compared with before PP. Only 2 patients did not tolerate the use of PP during spontaneous breathing. PP does not require the use of sedation to tolerate this position. In a letter to the editor, Pérez-Nieto et al. reported that in a multicenter retrospective series of 6 patients admitted to the ICU for severe ARDS of non-infectious etiology, the use of PP in non-intubated patients would avoid the need for intubation in 3 of 6 cases. Obviously, these results do not allow us to conclude on the utility of PP but rather indicate the potential of this technique in non-intubated patient (PEREZ-NIETO, Crit Care, 2020).

### Drawback of PP during spontaneous breathing

The mean duration on PP was 2 hr in spontaneously breathing patients in the study by Ding et al. (DING; Crit Care; 2020). For our study, to obtain an optimal benefit, we propose a minimum of two PP sessions during the day with a minimum cumulative time of 2.5 hr.

### Individual benefits

This study is a prospective randomized controlled interventional study.

To date, there is no recommendation for the use of PP in non-critical COVID-19 patients. The benefits are uncertain in these patients, and we believe that the use of this technique would decrease (as it seems to do for other patients with moderate ARDS) the time on oxygen therapy and the use of invasive or non-invasive ventilation and thus decrease the need for intensive care.

### Collective benefits

Improvement of oxygenation for COVID-19 patients resulting in reduced hospital stays, reduced congestion in ICUs and reduced mortality.

### Risks

One of the complications of COVID-19 is the evolution of severe ARDS.

The risk of PP is pressure on the face and knees, thorax and abdomen. These risks were observed in only sedated patients with neuromuscular blockades under invasive mechanical ventilation with PP for 16 hr. In spontaneously breathing, aware patients, patients will be able to move to avoid excess pressure. We can assume that the patients are ambulant and are able to adapt their positions according to their feelings.

In the PP studies in awake patients, no adverse events (AEs) have been reported. However, the following events may require a return to standard position: feeling of respiratory discomfort or any other uncomfortable feeling for the patient.

All these events will be only considered serious if they lead to worsening of the health condition that was present prior to PP.

The usual monitoring will be applied by the medical and paramedical teams of the enrolling wards. The teams will be free to determine whether the situation requires a change on supine position.

### Strategies to minimize risks

If an AE occurs, the patient would return to the supine position and semi-sitting position immediately. We will record the reasons for ending the procedure.

If an AE occurs during the prone procedure, we would follow the procedure described in Chapter 7.

# Research design

## Method

The control group will receive the usual care in each department involved in the study. The semi-sitting position in the bed or the chair is the usual care used in current practice for positioning.

In addition to usual care, the intervention group will benefit from a minimum of 2 prone position sessions during the day. The patient should lie in prone position for a minimum of 2 sessions during the daytime, with an objective of a cumulative time of at least 2.5 hr in the prone position during the daytime. Patients are encouraged to lie in the prone position as frequently and for as long as feasible, as soon as possible after randomization. They are assisted during positioning and given every necessary accessory to be as comfortable as possible (pillows, cushions, foam wedges).

This study is design to be pragmatic without disturbing or increasing the management of medical wards in the present context. It will not be possible to monitor the duration of PP at night because of overloading caregivers already under pressure during the pandemic.

Clinical and demographic data in relation to the hospitalization will be collected. No major physiological measurements will be performed in relation to the prone position because of the pragmatic concern of saving the time of caregivers during this epidemic period.

## Research-Specific Procedures

### Prone position

1. Preparation

Check that all cables and lines (if present) are mobile enough to allow the patient to perform the self-prone position.

Explain the procedure to the patient:

- Perform a minimum of 2 prone position sessions during the daytime.
- With an objective of a cumulative time of at least 2.5 hr in the prone position during the daytime. The objective is to lie as much as possible in the prone position if it is possible.
- Patients will be able to move their head as they desire.
- The leg can be slightly bent to discharge the hip.
- Patients can change their bent leg as they wish while the spine remains free.
- The arms can be along the body or one arm can bent or both arms can be bent as in the picture below.

[figure not shown]
The position should be as comfortable as possible for the patient.

1. How to process the positioning

- Note the date and time of the beginning of the prone position in the notebook (by the patient or by a staff member).
- Ask the patient to lie on the stomach and place the barrier to prevent a potential fall out of bed.
- Make sure the patient is comfortable and explain that they can move themselves in the bed but the back should always be kept free to avoid compression of the lungs in the back region.
- Patients can turn slightly to a more comfortable position.
- The call bell is given to the patient so that they can call a staff member for assistance before each position change.
- Explain to the patient to not position themselves in the PP or supine position but use the call bell so that someone can help and set the barriers (the patient is informed that they can call at any time to move around or go to the toilet and that the barriers are an essential safety measure for the study; if the patient perfectly self-positions in the prone position, barriers would be removed after the investigator’s decision; this must be recorded and justified in the medical record).
- Note the date and time of the end of the prone position in the notebook (by the patient or by a staff member).

Each day of hospitalization, at least two PP sessions during the day, with the objective to spend as much time as possible in PP if tolerated and a minimum of 2.5 hr of cumulative time in PP during the day.

A session of PP as long as possible at night. Patients will be encouraged to sleep in PP as much as possible at night, knowing that monitoring the number of hours will not be feasible in COVID-19 medical wards in the current context.

Bedridden patients who are not able to self-position to the prone position or with minimal assistance of one person will not be included in the study.

Barriers will be positioned to avoid the potential fall out of bed.

The patient will be allowed to choose the best PP as long as the back of the thorax is not compressed by the bed.

### Semi-sitting in a bed or chair

The semi-sitting position in the bed is a minimum of 30° inclination, not more than 60% to 70% to avoid compression of the abdomen.

The patient can be installed in a chair if they wish. In this case, the position will be mentioned in the notebook.

The prone position is not authorized during the daytime. It is allowed at night only if it is the natural sleeping position.

Lateral position is authorized outside the intervention periods if the patient wishes and will be recorded.

### Oxygen therapy modalities:

All oxygen therapies will be allowed: nasal cannula, facemask (with moderate or high oxygen concentration) and high-flow oxygen therapy.

In the intervention group: the clinician is free to choose the best modality taking into account the needs of the patient, and the interface should be the same before and during the prone position session.

In both groups: clinicians will be free of the indication for oxygen therapy, the modalities for weaning the oxygen therapy or changing the interface. Generally, oxygen therapy should administered with SpO_2_ <92% on room air, and its flow rate should be maintained at the minimum level to obtain SpO2 ≥ 92% (High Council of Public Health/*Haut Conseil de la santé publique relatif aux recommandations thérapeutiques dans la prise en charge du COVID-19*, complémentaire à l’avis du 5 mars 2020, 23 mars 2020; disponible à l’adresse: https://www.hcsp.fr/Explore.cgi/AvisRapports).

### Blood samples

No blood samples are required for the trial.

## Trial progress

### Inclusion

The screening log will be established by the investigators of each center. From this list, patients who are eligible (meeting all the inclusion criteria and none of the exclusion criteria) will be identified as well as the included patients. The preferential sleeping position (prone, supine or lateral position) will be reported to determine any potential bias of selection. When a patient has all the inclusion criteria and none of the exclusion criteria, a member of the study will propose the study to the patient. For women of childbearing age, we will perform a beta-HCG test to exclude pregnancy.

If after information is given and a time for reflection of 2 hr, written consent is obtained, the patient will be included in the study. Randomization will be performed on a dedicated website after a standardize SpO_2_ measurement (5-L oxygen mask test with a face mask for 5 min). The investigator will note the date, time and group of inclusion in the patient’s record. The patient will be considered included once they have given consent.

NB: Patients may be included without an exclusion period (see paragraph 11.4) in other studies, whether comparative or not, with or without drugs, except for a study comparing prone position outside ICUs.

### Patient follow-up

In both groups, the rate of patients usually sleeping in the prone position will be collected at the beginning of the study. These data will be considered in the data analysis.

After randomization, the intervention will be performed according to the procedure detailed above.

The criteria for prone position intolerance are as follows:

- feeling of respiratory discomfort or any other uncomfortable feeling for the patient.

If any of the above criteria appear, we will record them in the specific case report form.

The standard surveillance will be applied by staff members of the enrolling wards. The staff will be free to consider whether a patient should return to the supine position and/or increase the surveillance (e.g., more frequent monitoring of blood pressure, respiratory rate or SpO_2_). It will be recorded in the case report form (CRF).

In the interventional group, an evaluation of SpO_2_ will be performed at the first session (to evaluate the clinical improvement after the first session):

- SpO_2_ measurement before PP
- SpO_2_ measurement just before the return to supine position at the end of the first session.

| *Actions* | *Day 0*  *(****Inclusion visit)*** | *Positions* | *End of treatment*  *(hospital discharge or intensive care unit with mechanical ventilation)* |
| --- | --- | --- | --- |
| *Diagnosis of COVID-19* | *X* |  |  |
| *Written consent of the patient* | *X* |  |  |
| *Fax of inclusion to the research department* | *X* |  |  |
| *Medical history* | *X* |  |  |
| *Usual sleeping position* | *X* |  |  |
| *Positioning techniques (PP/semi-sitting)* |  | *X* |  |
| *Improvement of 2 points on the WHO ordinal scale* |  |  | *X* |
| *Adverse events* | *X* | *X* | *X* |

## Research duration

Inclusion period: Epidemic COVID-19 period

Duration of intervention: the study intervention will stop when one of the events is reached: initiation of non-invasive or invasive ventilation, death, or patient still hospitalized at day 28 without event. Patients hospitalized for > 28 days will continue to be followed in the study (rate of use of resuscitation, rate of use of non-invasive or invasive ventilation, death).

The duration of participation for each patient corresponds to the hospitalization duration (all wards combined), subject to AEs that would require a longer follow-up.

Total duration of participation in the study for the patient: length of hospitalization

Total duration of the study: 24 months

## Measures to reduce and avoid bias

### Randomization

Randomization will be centralized via a website.

Randomization will be stratified according to the following three parameters:

- **According to the center**
- **Body mass index (BMI) < 30 kg.m^-2^ or not**
- **SpO_2_ (measured by pulse oximetry) < 95% or ≥ 95% on 5-L/min test for 5 min before randomization**

How SpO_2_ will be measured for stratification will be standardized: in patients already included but not yet randomized, SpO_2_ will be systematically measured after 5 min of 5-L/min nasal O_2_ therapy with a moderate concentration mask.

A randomization list will be established beforehand by a clinical study technician, by permuted blocks, whose size will remain unknown to the investigators. The strata are as follows:

**1. BMI < 30 kg.m^-2^ and SpO_2_ ≥ 95%**

**2. BMI < 30 kg.m^-2^ and SpO_2_ < 95%**

**3. BMI ≥ 30 kg.m^-2^ and SpO_2_ ≥ 95%**

**4. BMI ≥ 30 kg.m^-2^ and SpO_2_ < 95%**

The treatment arm will be assigned by randomization.

### Blinding methods

Blinding the patients and the investigator is not technically feasible.

## Data input in the CRF used as source data

| **Evaluations** | **Variables** |
| --- | --- |
| - Duration of prone position per session  - Number of prone position sessions  - Intolerance to prone position  If yes, specify the reason | Minutes  Continuous  Yes/No  In clear |
| - Semi-sitting in a chair  - Semi-sitting in bed  - Walking around  - Lateral position | Yes/No  Yes/No  Yes/No  Yes/no |
| - In interventional group: response to PP at first session  SpO_2_ before PP  SpO_2_ just before the return to the supine position | %  % |
| - 7-level ordinal scale (appendix 4) | 1 to 7 |

All other data will be collected from the patient’s hospital record.

## Rules for definitive or temporary termination

### Withdrawal of a patient’s participation in the research

Patients will be able to withdraw their consent and to leave the trial at any time and for any reason. In the case of premature withdrawal, the investigator must specify the reason.

The investigator will be able to definitively or temporarily stop the patient’s participation in the trial for any reason according to what is in the patient’s best interests, especially in the case of serious AEs.

The patient’s withdrawal shall not affect their standard of care for their pathology. In the case of an AE, whether serious or non-serious, specific follow-up can be considered, depending on the severity. The supervisory board shall then determine the conditions of follow-up on a case-by-case basis.

### Termination of part of the research or the research as a whole

The study can be suspended or prematurely interrupted in the case of unexpected serious AEs, requiring examination of the outcome for all patients already included.

If PP has led to the occurrence of cardiac arrest, we will report this to the sponsor who can suspend the study if they consider it necessary.

Likewise, unexpected events that would lead to the impossibility to achieve the primary and secondary endpoints may lead the sponsor to interrupt the study prematurely.

Orléans Regional Hospital reserves the right to interrupt the study at any time if the inclusion objectives are not reached.

# Drugs administered

## Authorized treatments

All

## Unauthorized treatments

None

## Emergency treatment

If PP induces a major decrease in SpO2 for more than 5 min or a non-resolving tachycardia despite a return to the classical sitting position or an adaptation of the oxygenation or non-invasive ventilation parameters by the clinician in charge of the patient, we will record this event as a non-serious AE if the supine position improves this parameter. However, if, despite the supine positioning, the patient does not show improvement of respiratory parameters, we will record a serious AE related to the PP.

If the respiratory signs deteriorate significantly, the use of non-invasive ventilation with 2 pressure levels or intubation will be possible if the clinician in charge of the patient considers it necessary. If intubation is considered unreasonable because of the evolution of the disease and vital parameters, although the patient would have initially received treatment in the ICU, appropriate care will be implemented for comfort in accordance with the practices of each department.

# Safety assessment

## Definitions

- **Adverse event (AE)**: any untoward occurrence in a patient or clinical investigation subject who is the subject of research involving humans. The event does not necessarily have a causal relationship with this treatment.
- **Adverse effect**: undesired harmful effect resulting from the intervention
- **Serious AE**: An adverse event or suspected adverse reaction is considered "serious" if, in the view of either the investigator or sponsor, the following outcomes occur:
  - Death
  - A life-threatening AE
  - A persistent or significant incapacity or substantial disruption of the ability to conduct normal life functions
  - Inpatient hospitalization
  - Prolongation of existing hospitalization
  - Congenital anomaly/birth defect
  - Requires intervention to prevent permanent impairment or damage
- **Unexpected AE**: adverse effect that is not consistent with the information given in the investigator’s information sheet
- **New information**: Any new information that may lead to a re-evaluation of the risk/benefit ratio of the research, change the research or stop or modify the research.

## Adverse event reporting

The monitoring and reporting of incidents and the risk of incidents resulting from participation in the trial will be declared via the Orléans Regional Hospital regular vigilance network with the following specificities.

##### Related to protocol:

The following event will automatically be considered as a serious AE of special interest:

- For prone position group:
  - Cardiac arrest
  - Persistent desaturation despite a return to the previous position without desaturation or adaptation of oxygenation
  - Unresolved hypotension by a return to the previous position without hypotension
  - Bradycardia < 45 bpm persisting for > 1 min
  - Catheter disconnection
  - Pressure point in the areas at risk
  - Adverse event exclusively due to the hospitalization
  - Catheter disconnection without clinical impact
  - Sinus tachycardia
  - Transitory desaturation resolving within 3 min
  - Death not related to prone position

Only cardiac arrest during a prone position session is subject to immediate reporting to the sponsor, using the form provided for this case by fax to [name] or by e-mail to [[contact]](mailto:[contact]).

The investigator must also attach the following to the cardiac arrest report whenever possible:

- A copy of the prolongation of hospitalization
- A copy of the autopsy report if applicable
- A copy of all results of additional exams including relevant negative results, with the normal laboratory values
- Any other document considered useful and relevant

These documents will be anonymized and will identified by the identification number of the patient.

ARDS induced by COVID-19 is a life-threatening disease; the risk of death is higher than in the standard population hospitalized in the enrolling departments. We will not consider the death as an AE unless it is attributable to one of the AEs listed above in association with the study’s intervention.

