***How to deal with an AE:***

If an AE occurs, the investigator may:

- Continue the strategy
- Temporally or permanently stop the strategy

In addition, monitoring will be intensified and all measures to prevent the occurrence of an AE will be taken by the investigator with an immediate and explicit notification to the sponsor.

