### Supervisory board

No supervisory board was considered necessary.

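### Section 7.2 makes 11 events automatically serious in the prone group only, and contradicts other text on seriousness, death, reporting and oversight, so serious-event counts are not comparable between arms

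*Protocol*

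**What the plan says.** Section 7.2 of the protocol, under the sub-heading on events related to the protocol, states: "The following event will automatically be considered as a serious AE of special interest". One list follows, labelled as applying to the prone group. It has 11 items. The first six are cardiac arrest, persistent desaturation, unresolved hypotension, bradycardia, catheter disconnection and pressure points. The last five are events that stem only from the hospital stay, catheter disconnection with no clinical effect, sinus tachycardia, "Transitory desaturation resolving within 3 min", and death unrelated to proning. There is no list for usual care.

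Other places speak to the same matters:

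- Section 6.3, on a major desaturation of more than 5 min or a tachycardia that does not resolve: "we will record this event as a non-serious AE if the supine position improves this parameter".
- Section 4.4 (Risks): events that call for a return to the standard position are serious only if the patient's prior condition worsens.
- Section 7.1: an adverse event needs no causal link, and seriousness depends on listed outcomes, death among them.
- Section 7.2, closing sentence on death: "We will not consider the death as an AE unless it is attributable to one of the AEs listed above", with the further condition of an association with the intervention.
- Section 7.2, on reporting: "Only cardiac arrest during a prone position session is subject to immediate reporting to the sponsor".
- Section 7.2, on how to deal with an adverse event: measures are to be taken "by the investigator with an immediate and explicit notification to the sponsor".
- Section 5.7, on follow-up of adverse events after withdrawal: "The supervisory board shall then determine the conditions of follow-up on a case-by-case basis".
- Section 7.2, last heading: "No supervisory board was considered necessary". The front matter likewise marks the supervisory board as not applicable.

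**The concern.** A count of serious events can be compared between arms only if the same rule decides seriousness in both. Here a prone patient with a short sinus tachycardia has a serious event by rule, while a control patient with the same tachycardia has one only if a section 7.1 criterion is met. The trial is unblinded (section 5.5), so nothing downstream removes this difference.

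Within the prone arm, an investigator cannot follow all the rules at once. Two sites reading the same protocol could classify the same event in opposite ways and could differ on what must reach the sponsor immediately.

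Classification also has consequences during the trial: section 5.7 makes unexpected serious adverse events a ground for suspending it. The protocol does not say whether a listed event would count as unexpected, but a seriousness rule that is unclear makes that decision harder.

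**Working it through.** The safety section contains no computed figure, so the check is mainly a side-by-side reading.

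**1. Seriousness of the last five list items**

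| Item (paraphrased) | Section 7.2 list | Other text | Result |
|---|---|---|---|
| Sinus tachycardia | Automatically serious | Section 6.3: even a non-resolving tachycardia is non-serious if lying supine improves it; section 4.4 also makes seriousness conditional | Direct conflict |
| Desaturation over within 3 min | Automatically serious | Section 6.3: a desaturation of more than 5 min is non-serious if lying supine improves it | Direct conflict, by comparison: the shorter event is classed as graver |
| Death unrelated to proning | Automatically serious | Section 7.2 closing sentence: such a death is not an adverse event | Direct conflict inside one section |
| Disconnection with no clinical effect | Automatically serious | Section 7.1: need not meet any seriousness outcome; the list also has disconnection as a separate item | Mismatch with the definition |
| Event due only to the hospital stay | Automatically serious | Section 7.1: need not meet any seriousness outcome; the sub-heading is about events related to the protocol | Mismatch with the definition |

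That is 3 of 11 items in direct conflict and 2 of 11 at odds with the general definition. The other six are not disputed: persistent desaturation, for example, agrees with section 6.3, which records a serious event when supine positioning does not help.

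**2. Death.** Section 7.1 makes death a seriousness outcome with no causality test. The list makes unrelated death serious. The closing sentence removes it from adverse events altogether. No reading satisfies all three.

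**3. Reporting.** One sentence limits immediate reporting to a single event in a single circumstance. The other, under a heading that begins from the occurrence of an adverse event, asks for immediate notification with no such limit.

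**4. Oversight.** Section 5.7 gives a decision to a board that two other places say was not set up.

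**5. Size of the arm difference (illustration with assumed rates).** Inputs from the protocol: 268 patients (section 8.2) and 1:1 allocation (synopsis), so 268 / 2 = 134 per arm. Assumptions, not in the documents: a true serious-event rate s = 5% in both arms, and a rate r of minor listed events that is equal in both arms, independent of s, and counted as serious in the prone arm only.

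Apparent prone rate = 1 − (1 − s)(1 − r). Chance of a nominally significant difference = Φ[(Δ − 1.96·SE0)/SE1], with SE0 = √[2p̄(1 − p̄)/134] and SE1 = √[(p1(1 − p1) + p2(1 − p2))/134].

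For r = 10%: 1 − 0.95 × 0.90 = 14.5%, so Δ = 9.5 points and p̄ = 9.75%. SE0 = 0.0362, SE1 = 0.0358, and (0.0950 − 0.0710)/0.0358 = 0.67, giving about 75%.

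| Assumed r | Apparent rate, prone vs control | Chance of a significant difference |
|---|---|---|
| 5% | 9.8% vs 5.0% | about 32% |
| 10% | 14.5% vs 5.0% | about 75% |
| 20% | 24.0% vs 5.0% | over 99% |

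The true difference is zero in every row.

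**The case against.** The strongest reply is that most of this comes from one lost line. The last five items read as benign counterparts of the first six: harmless against ordinary disconnection, transient against persistent desaturation. Unrelated death fits the closing sentence if it belongs among events not counted as serious. With a heading to that effect, the conflicts on seriousness and death disappear together. This is plausible and may well be the cause. It remains an inference: no such heading is in the text, and sites work from the text. If a line was lost, the correction is still needed. That reading also leaves the reporting rule, the board and the prone-only scope untouched.

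A second reply is that some items are prone-specific by nature. Persistent desaturation and unresolved hypotension are defined by a return to the previous position, and controls are not proned by day. That stands for those items. It does not explain why bradycardia, tachycardia or cardiac arrest should be listed for one arm only.

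Third, a reader might infer that harms cannot be compared at all. The documents do not support this. Section 7.1 covers any participant, the schedule in section 5.3 has an adverse-event row without arm restriction, and death, intubation, non-invasive ventilation and ICU transfer are compared by arm (section 8.1). Nor do the position worksheets in Appendices 2 and 3 prove that controls lack adverse-event recording: the control sheet is an example for noting positions.

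Fourth, a reader might infer from the missing board that nobody can act on a signal. That is not so: the investigator may stop a patient's participation or the strategy, the sponsor may suspend the study, and incidents go through the hospital's vigilance network (sections 5.7 and 7.2).

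Finally, comparing adverse events is not a stated objective, and their tabulation may be left to a statistical analysis plan not available here. An analysis plan could tabulate events, but it could not undo a seriousness rule applied differently at the bedside.

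**Conclusion.** The point holds in a bounded form. As written, section 7.2 applies an automatic seriousness rule to 11 events in the prone group only. Three of those items contradict section 6.3 or section 7.2 itself, and two more fall outside what section 7.1 requires. The immediate-reporting rules conflict, and section 5.7 names a board that does not exist. It would overstate the case to say that five items conflict directly.

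The consequence is confined to counts of serious adverse events and events of special interest, which are not comparable between arms. The primary analysis and the other between-arm comparisons are unaffected. The direction of the distortion follows from the text, towards more serious events under proning; its size does not. The figures of 32% to over 99% rest wholly on assumed event rates and show only that the effect need not be small.

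**What to change.** The sponsor should reconcile sections 4.4 (Risks), 6.3, 7.1 and 7.2 so that each event, death included, has one seriousness classification and there is one immediate-reporting rule. Which of the conflicting rules prevails is for the sponsor; this review does not choose. If a heading was lost before the last five items, restoring it would settle part of this.

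Apply the same seriousness definition and the same adverse-event page to both arms. Keep items defined by a return from the prone position as prone-specific and label them so. Tabulate the shared events by arm. In section 5.7, replace the supervisory board with the body that will actually decide on follow-up.

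The cost is protocol wording, a common adverse-event page and slightly more recording in the usual-care arm. Sample size and the primary analysis do not change.
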